**Methods and analysis:**

This three-arm randomised controlled trial will recruit participants 18–85 years, endorsing ≥3 symptoms on the Yale Food Addiction Scale (YFAS) 2.0, with body mass index >18.5 kg/m^2^. Addictive eating symptoms are assessed at baseline (pre-intervention), 3 months (post-intervention) and 6 months. Other outcomes include dietary intake and quality, depression, anxiety, stress, quality of life, physical activity and sleep hygiene. Using a multicomponent clinician-led approach, the active intervention consists of five telehealth sessions (15–45 min each) delivered by a dietitian over 3 months. The intervention uses personalised feedback, skill-building exercises, reflective activities and goal setting. Participants are provided with a workbook and website access. The passive intervention group receives the intervention via a self-guided approach with access to the workbook and website (no telehealth). The control group receives personalised written dietary feedback at baseline and participants advised to follow their usual dietary pattern for 6 months. The control group will be offered the passive intervention after 6 months. The primary endpoint is YFAS symptom scores at 3 months. A cost–consequence analysis will determine intervention costs alongside mean change outcomes.

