To the authors’ knowledge, the TRACE Programme is the first MI-based telehealth intervention used in combination with personalised coping skills training for the management of addictive eating in adults. The aim of the current study is to determine the efficacy of a telehealth intervention (active intervention) to reduce symptoms of addictive eating in adults, relative to passive intervention and control (no intervention) groups. It is hypothesised that both the active and passive intervention groups will achieve a reduction in addictive eating symptoms relative to the control group. Potential moderators (eg, participant sociodemographics) and mediators (eg, physical activity, diet and sleep) of intervention efficacy will also be evaluated.

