### Study procedure

Prospective participants will complete the eligibility survey. This will include demographic questions (eg, sex, postcode, marital status, level of education, employment status); the YFAS 2.0^6^ to confirm endorsement of ≥3 addictive eating symptoms; and the EDE-QS^31^ to confirm the absence of purging behaviours. While not necessary to determine eligibility, the Patient Health Questionnaire-8 (PHQ-8),^63^ Generalized Anxiety Disorder-7 (GAD-7),^60^ Perceived Stress Scale-4,^61^ Patient Activation Measure 13^64^ and two questions relating to previous treatments sought for addictive eating will also be completed by potential participants. These questions have been specifically added to extend our previously reported research^65^ regarding the types of individuals recruited into interventions for addictive eating.

Participants deemed eligible will proceed to the online consent form (figure 1—overview of study schedule). Participants will be given a 2-week period to consider participation. After this time, a member of the research team will contact any individuals via email who have not completed the consent form to determine their interest in participating. Following this, no other contact will be made. Participants who provide electronic written consent will complete the baseline assessment surveys measuring dietary intake and eating habits, traits associated with personality and risk of addictive behaviour, quality of life and healthcare service utilisation (table 1—schedule of measurements). The surveys take approximately 40 min to complete. On completion of baseline surveys, participants will be randomly allocated to one of three groups (group 1: active intervention; group 2: passive intervention; or group 3: control; see the Intervention section) and informed of their group allocation via email.

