### Outcome measures

All outcome measures are completed at baseline, 3 months (immediate post-active intervention period) and 6 months (follow-up) via online surveys. The same survey tools will be used at each time point. Participants will receive assessment reminders by email (reference to where data collection forms can be found is included in online supplemental material 2).

10.1136/bmjopen-2022-064151.supp2Supplementary data

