### Sample size

The sample size for the study was calculated based on data from the feasibility study,^24^ given the absence of other intervention studies. Through guidance with statisticians, a large effect size was chosen and needed to enable the possibility of a clinically meaningful result. A clinically meaningful difference in symptoms of addictive eating was selected as a decrease of two symptoms, given this would correspond to a change in severity classification on the YFAS 2.0 tool. To detect a mean two-unit difference (SD=2.2) in the YFAS symptoms between the active intervention group and the passive intervention group or control group and using a standardised effect size of d=0.91, a sample size of 32 individuals per group (total sample size n=96) is required to detect this change with a power of 0.90 and a type 1 error rate set at 0.025 to account for multiple testing. However, allowing for a 30% dropout rate from the pilot, a sample size of 46 individuals per group (total sample size n=138) would be required. Therefore, a total sample size of 150 individuals, with 50 per group, was chosen to remain conservative.

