### Statistical analysis plan

Data analysis will be conducted by a researcher blinded to the intervention conditions. Descriptive statistics of sample characteristics will be presented. For the primary YFAS outcome, a linear mixed model (LMM) will be based on a model with main effects for group (active intervention, passive intervention, control) and time (treated as categorical at levels baseline, 3 and 6 months), and the group-by-time interaction. An unstructured residual covariance structure will be used to allow for correlation between the repeated measurements for a subject. The primary outcome effect will be reported as the difference between means at baseline and 3 months, with a 95% CI for the difference. Mental health condition and BMI will be examined for possible moderating effects on the effect size, and if so, adjustment for them will be carried out. Secondary descriptive analysis will be carried out to identify whether specific symptoms were predominantly associated with reductions in YFAS score.

A secondary outcome will be a categorical variable, clinically significant change from baseline to 3 months, where significant requires a reduction of two or more symptoms in the YFAS. This will be analysed using logistic regression with group being the only factor. Additional secondary outcomes will include dietary outcomes (average daily energy intake, proportion of total energy intake contributed by core food and non-core food intake, macronutrient intake, micronutrient intake and overall diet quality) and mental health status (depression, anxiety and stress scores). These will also be analysed using LMMs as per the approach above. All available data will be used with no imputation of missing values at 3 and 6 months; however, baseline scores will be kept. The participants will be analysed according to their allocated randomisation group consistent with an intention-to-treat analysis. Statistical significance will be set at 0.05.

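### The stated primary effect is, read literally, a change from baseline to 3 months, while the aim, hypothesis and sample size concern differences between arms

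*Protocol article*

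**What the plan says.** The Statistical analysis plan section fits a linear mixed model with group, time "and time (treated as categorical at levels baseline, 3 and 6 months), and the group-by-time interaction". It then fixes what will be reported: "The primary outcome effect will be reported as the difference between means at baseline and 3 months, with a 95% CI for the difference". The two means in that sentence are distinguished by time only.

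Elsewhere the article is comparative:

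- **Aim (end of Introduction):** the active intervention is meant "to reduce symptoms of addictive eating in adults, relative to passive intervention and control (no intervention) groups".
- **Hypothesis (same paragraph):** "both the active and passive intervention groups will achieve a reduction in addictive eating symptoms relative to the control group".
- **Sample size:** "To detect a mean two-unit difference (SD=2.2) in the YFAS symptoms between the active intervention group and the passive intervention group or control group".
- **Abstract:** "The primary endpoint is YFAS symptom scores at 3 months", which names a score at a time point and again no contrast.

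On timing, Study procedure places the YFAS in the eligibility survey, "to confirm endorsement of ≥3 addictive eating symptoms". Table 1 ticks it at eligibility screening, 3 months and 6 months, with no tick at t1. The Outcome measures section says instead: "All outcome measures are completed at baseline, 3 months (immediate post-active intervention period) and 6 months (follow-up) via online surveys".

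**The concern.** The one sentence that defines the reported primary effect does not describe the quantity the trial was designed to estimate. An analyst who followed it to the letter could report the active arm's baseline-to-3-month change, or the change averaged over all arms, with its interval, and be compliant. Neither figure compares treatments.

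A pre-post change is a weak measure here for two further reasons. It includes whatever would have happened without the programme. It also starts from a score that had to reach 3 for the person to be enrolled. People selected for a high reading tend to read lower next time, so some fall is expected in all three arms, control included, even if nothing works. A confidence interval for that change may exclude zero without a treatment effect.

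**Working it through.** **1. Which quantity was the trial sized for?** Inputs from the Sample size section: difference 2, SD 2.2, power 0.90, type 1 error 0.025, 30% dropout.

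- Standardised effect: 2 / 2.2 = 0.909, matching the stated 0.91.
- Two-sample normal approximation, two-sided: n = 2 × SD² × (z₀.₉₈₇₅ + z₀.₉₀)² / difference² = 2 × 4.84 × (2.241 + 1.282)² / 4 = 30.04, rounded up to 31 per group.
- Exact two-sided t test: power 0.897 at 31 and 0.907 at 32, so 32 per group. This is the stated figure.
- One-sided 0.025: 26 (normal) or 27 (t). Does not reproduce.
- Paired, within one arm, same SD and an assumed correlation of 0.3 to 0.8: 24 down to 9. Does not reproduce.
- Dropout: 32 / 0.70 = 45.7, so 46 per group and 138 in total, as stated.

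The plan was sized for a difference between arms.

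**2. Which contrasts do the sections name?**

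| Section | Active v passive | Active v control | Passive v control |
|---|---|---|---|
| Aim | yes | yes | no |
| Hypothesis | no | yes | yes |
| Sample size | yes | yes | no |
| Reported primary effect | none named | none named | none named |

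The 0.025 in the sample size is 0.05 / 2, which fits two comparisons. The analysis section uses a 95% interval and a 0.05 threshold.

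**3. How much could a pre-post change move without treatment?** The article gives neither the score distribution of the people screened nor a retest correlation, so this rests on assumptions: a normal score rounded to the 0–11 range, selection at 3 or more, no treatment effect, SD 2.2 or 3.0, retest correlation 0.5 to 0.85, and 35 completers per arm (50 × 0.70).

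| Assumed mean in those screened | Expected fall (symptoms) | Chance that a within-arm 95% CI shows a fall |
|---|---|---|
| 2 | 0.35 to 1.25 | 32% to 86% |
| 4 | 0.15 to 0.73 | 11% to 34% |
| 6 | 0.04 to 0.34 | 4% to about 10% |

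The nominal chance in that direction is 2.5%.

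A closed form for a continuous normal score agrees in scale: fall = (1 − ρ) × SD × φ(z) / Φ(−z), with z = (3 − mean) / SD. For mean 4, SD 2.2 and ρ = 0.7, z = −0.455 and the fall is 0.3 × 2.2 × 0.533 = 0.35.

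**4. Does the shift affect a comparison of arms?** Selection happens before randomisation, so the expected fall is the same in each arm. Subtracting one arm's change from another's removes it in expectation.

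**5. What does the model estimate?** With baseline as the reference level of time, the group-by-time term at 3 months is the between-group difference in change from baseline. The between-group difference in 3-month means is that term plus the group main effect. Randomisation gives both the same expectation, but they are different estimates, so the definition should name one.

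**6. Power under the restated effect.** Taking the plan's SD of 2.2 for the compared quantity, as its own calculation does, 35 completers per arm give power 0.93 for a 2-symptom difference at two-sided 0.025.

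**The case against.** The sentence follows directly on a model with a group-by-time interaction, and it does not say that the change is to be judged within each arm. The aim, hypothesis and sizing are comparative, and the logistic analysis of the 2-symptom response has group as its only factor. Moderators are to be examined for their influence on the effect size, which presupposes a group effect. The likely intention is therefore the change compared across groups, shortened in a condensed article.

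Most of this stands. The model can supply the right contrast and the intent is clear. A reader might infer that the investigators plan to claim efficacy from a pre-post interval in one arm. Nothing in the article says so. What does not stand is that the sentence may be left alone: the article states the primary effect explicitly, and no sentence states the group comparison as that effect.

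A reader might also infer a substantial regression-to-the-mean bias by applying the Introduction's 15%–20% prevalence of 3 or more symptoms to an SD of 2.2, which gives falls of 0.31 to 1.03 for retest correlations of 0.7 to 0.9. The article does not support that model. It implies a mean of 0.7 to 1.1 with 30% to 37% of people below zero on a 0–11 scale, and an SD after selection of about 1.0 where the plan uses 2.2. Participants are also volunteers responding to advertising, not a cross-section of adults. With a source mean of 4 to 6, SD 2.2 and correlations of 0.7 or more, the fall is about 0.04 to 0.35.

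**Conclusion.** The definition of the primary effect is wrong as written and should be corrected before analysis. That conclusion needs no assumptions: the sentence names a contrast over time, while the aim, the hypothesis and a sample size that reproduces as a two-sample test are between arms.

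Regression to the mean is a reason not to rely on a pre-post change. It is not a second defect. Its direction follows from entry on the same score, provided that the screening YFAS serves as baseline, as Table 1 and Study procedure indicate. Its size, about 0.04 to 1.25 symptoms across the assumptions tried, cannot be narrowed from the article and may be small if enrolled people score well above 3. If the YFAS were in fact repeated at t1, the shift would shrink but the definition would still lack a group comparison.

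It does not follow that the model is unsuitable, that the trial is too small, or that a between-arm result from it would be biased by the entry rule.

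**What to change.** Replace the sentence with wording such as:

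> The primary effect is the between-group difference in mean change in YFAS symptom score from baseline to 3 months (the group-by-time contrast at 3 months in the LMM), for active versus passive and active versus control, each with a confidence interval at the level matching the 0.025 per-comparison error rate used for sizing. Within-group changes are descriptive only.

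That level is 97.5%. In addition:

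- State how the passive-versus-control comparison in the hypothesis is handled, since the sample size does not cover it.
- Bring the abstract's statement of the endpoint into line.
- Reconcile the Outcome measures section with Table 1 by stating that baseline YFAS is the screening measurement.

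The cost is a few sentences. The model, data collection, number of participants and the figures of 32 and 46 per group are unchanged.

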### Randomisation and blinding

Following completion of baseline assessments, participants will be stratified into four groups by sex and mental health status (presence or absence, based on either depression scale PHQ-8 scores ≥15 or below 15, or anxiety scale GAD-7 scores ≥11 or below 11). Participants within each of these four groups will be randomised to one of the three study groups in equal ratios using permuted block randomisation, with block sizes of six. Randomisation will promote group balance on these variables shown to be important in past cross-sectional research (for example, 7 8 10 65). The randomisation sequence will be generated by an independent statistician and implemented by a designated study coordinator. The allocation list will be stored in a password-protected computer file and accessed only by the study coordinator.

Due to the telehealth nature of the active intervention, blinding of participants and dietitians to intervention group allocation in this study will not be possible. However, several strategies will be employed to reduce the risk of bias. First, participants will only be provided with partial information on the study hypotheses. Second, all communication between participants and research staff during the period of intervention (ie, scheduling concerns, questions regarding the intervention) will be done directly between participants and the ‘study coordinator’ or their respective ‘telehealth clinician’. Lastly, statistical analyses will be conducted by researchers who are blind to group allocation prior to analysis.

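### Randomisation is stratified by sex and mental health status, but the stated primary model omits sex and admits mental health only if the data show moderation

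*Protocol article*

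**What the plan says.** Under Randomisation and blinding, the Protocol article states that "participants will be stratified into four groups by sex and mental health status". Mental health status is defined as presence or absence, "based on either depression scale PHQ-8 scores ≥15 or below 15, or anxiety scale GAD-7 scores ≥11 or below 11". I read presence as meeting either cut-off. Allocation within each stratum is "in equal ratios using permuted block randomisation, with block sizes of six". The reason given is that "Randomisation will promote group balance on these variables shown to be important in past cross-sectional research".

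Under Statistical analysis plan, the primary analysis is "a model with main effects for group (active intervention, passive intervention, control) and time (treated as categorical at levels baseline, 3 and 6 months"), plus the group-by-time interaction. Baseline is thus one of the repeated responses, and "An unstructured residual covariance structure will be used to allow for correlation between the repeated measurements for a subject". The primary effect is the baseline to 3-month difference in means with a 95% CI. Sex does not appear in the section. On other covariates the rule is: "Mental health condition and BMI will be examined for possible moderating effects on the effect size, and if so, adjustment for them", the sentence ending by saying that this adjustment is then made. The section does not say which test or threshold counts as finding moderation, whether the adjustment is a main effect or an interaction, or whether the mental health variable is the randomisation stratum.

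The secondary mixed models follow the same approach. For the responder outcome (a reduction of two or more symptoms): "This will be analysed using logistic regression with group being the only factor".

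**The concern.** There are two problems.

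First, the primary model is not fixed in advance. Whether mental health and BMI enter it depends on a look at the group-by-covariate effect in the outcome data. If they enter as interactions, the group term also changes meaning: it becomes an effect at a particular covariate value.

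Second, the criterion does not fit its purpose. Effect modification is described by an interaction. A stratification factor belongs in the model because it constrained the allocation, whether or not it modifies the effect. Under the stated rule BMI, which did not constrain allocation, can enter the model, while sex, which did, cannot.

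At stake are the pre-specification of the primary estimate and, possibly, some precision. If the strata predict the analysed contrast, stratified blocks remove that variation from the difference between arms, but an unadjusted model keeps it in the residual variance, so the standard error is larger than the design warrants.

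**Working it through.** **Inputs from the Protocol article (Sample size):** difference 2 symptoms, SD 2.2 (d = 0.91), alpha 0.025, power 0.90, 30% dropout, 150 randomised. Completers: 150 × 0.70 = 105, or 35 per arm.

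**Assumptions, not in the document:** within-person correlation 0.5; 20% men; 40% in the mental-health stratum; moderation tests at 0.05; and the share R² of the variance of change in YFAS score that the strata explain.

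**1. The plan's own figure.** Normal approximation, two-sided: n = 2 × (2.241 + 1.282)² × (2.2/2)² = 2 × 12.41 × 1.21 = 30.03, so 31 per group. The exact t calculation with d = 0.91 gives 32 (power 0.907). Then 32/0.70 = 45.7, so 46. The stated 32 and 46 reproduce. They come from an unadjusted two-group comparison, so this point does not change the required sample size.

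**2. Strata that affect only the level of YFAS.** Baseline is a response and the effect is a change contrast, so a time-constant effect of sex or mental health cancels. With 35 per arm and complete data, SE = √[2 × 2(1 − 0.5) × 2.2² / 35] = √(9.68/35) = 0.526. Generalised least squares for the three-visit model gives 0.5259 with no strata and 0.5259 with the strata as main effects. Adding main effects alone therefore changes nothing.

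**3. Strata that predict change.** The unadjusted SE is too large by the factor 1/√(1 − R²), and a nominal 0.05 test runs at 2[1 − Φ(1.96/√(1 − R²))]. These were checked by simulation with stratified blocks of six and 105 completers (4,000 trials per scenario; Monte Carlo error of coverage about 0.3 percentage points).

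| R² of change (assumed) | SE factor, formula | SE factor, simulated | Actual size, formula | Coverage, unadjusted / adjusted (simulated) |
|---|---|---|---|---|
| 0% | 1.000 | 0.999–1.000 | 0.050 | 94.3–95.2% / 94.2–95.0% |
| 2% | 1.010 | 1.010 | 0.048 | 94.9% / 94.8% |
| 5% | 1.026 | 1.026 | 0.044 | 94.8% / 94.4% |
| 10% | 1.054 | 1.054 | 0.039 | 95.7% / 94.6% |
| 20% | 1.118 | 1.119 | 0.028 | 97.2% / 95.2% |

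If the contrast were instead the 3-month means alone, the strata's effect on level would matter. The simulated excess is then about 3%, 6% and 12% for strata explaining 5%, 10% and 20% of the 3-month variance.

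**4. The conditional rule.** With two independent tests at 0.05 and no true moderation, the chance that the model changes is 1 − 0.95² = 0.0975. Simulation of 10,000 null trials per scenario (simple allocation, 35 per arm) gave 9.3% to 10.0%. On the same simulated data, the type I error of one pairwise test was:

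- fixed unadjusted model: 0.056, 0.053 and 0.050 (covariate R² of 0, 0.1 and 0.2);
- rule applied with main effects: 0.056, 0.052 and 0.051;
- rule applied with interactions: 0.058, 0.053 and 0.052.

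The largest difference from the fixed model in any scenario is under 0.002.

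**The case against.** The strongest counter-case has four parts.

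- *Width.* A reader might infer that the confidence intervals are certainly too wide. The document does not support that. Its stated reason for stratifying is cross-sectional importance, which concerns the level of addictive eating and not change over three months, and level effects cancel in the primary contrast. This objection stands, so the excess has to be given as a range starting at nil.
- *False positives.* A reader might infer that a data-chosen model inflates type I error. The simulation shows no material inflation, and any error from omitting the strata is conservative. Nor is the moderation check post hoc: both moderators are named in advance, and the analyst is blinded to group. This also stands. The 10% figure counts changes of model, not wrong conclusions.
- *Silence.* A condensed article may leave covariate lists to a fuller plan. That has some force for sex, but not for the conditional rule or for the responder model with group alone, both of which are explicit.
- *The remedy.* A time interaction has no meaning in a single-outcome logistic model, and adding covariates there makes the odds ratio conditional. That is correct, and the fix allows for it. It can also be said that, for the depression and anxiety outcomes, the stratum is a dichotomy of the baseline response. This does not affect the primary model. For those outcomes allocation is still random within the stratum, and regression to the mean makes the stratum likely to predict change.

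**Conclusion.** The point holds as a matter of pre-specification and of matching the analysis to the randomisation. The stated primary model leaves out both stratification factors, cannot admit sex, and admits mental health and BMI on a data-dependent criterion that is wrong for a stratifier. Under two independent 0.05 tests, the model would change by chance in about 10% of trials with no moderation.

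The effect on precision is uncertain. It is nil if the strata do not predict change in YFAS score, about 3% and 5% extra CI width if they explain 5% and 10% of its variance, and 12% if they explain 20%. The document gives no figure for that share, so these are scenarios and not estimates. The direction is conservative. Neither certain loss of precision nor an excess of false positives is shown, and the sample size is unaffected. The change is still worth making before unblinded analysis, because it costs almost nothing.

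**What to change.** - **Primary mixed model:** include sex and the randomisation mental-health stratum (PHQ-8 ≥15 or GAD-7 ≥11) as fixed effects, each with a time interaction, regardless of any test. The time interaction is needed because main effects alone leave the change contrast as it was (step 2).
- **Secondary mixed models:** the same terms.
- **Responder logistic regression:** add the two strata as main effects only. State that the odds ratio is then conditional on them, or report a standardised marginal effect.
- **Moderation:** delete the conditional clause on adjustment. Report moderation by mental health and BMI as separate exploratory group-by-time-by-moderator analyses that do not alter the primary model.

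The cost is wording plus, in each mixed model, six mean parameters (two factors × three visits). Sex, PHQ-8 and GAD-7 are already collected at eligibility screening (Table 1). If the strata turn out not to predict change, the simulated precision loss from adjusting is below 0.1% of the SE.

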### Primary outcomes

#### Addictive eating symptoms and severity

The YFAS 2.0^6^ will be used to assess the change in addictive eating symptomatology and severity. The YFAS 2.0 is a validated self-report 35-item questionnaire. The YFAS 2.0 asks participants to think of specific foods they have had difficulty controlling the consumption of within the past 3 months (eg, ice cream, chocolate, chips, hamburgers). The YFAS 2.0 provides an addictive eating symptom score ranging from 0 to 11. Additionally, two items assess clinically significant impairment or distress from eating. A ‘food addiction diagnosis’ can be given when ≥2 symptoms are endorsed, and clinically significant impairment or distress is present. However, for the purpose of this study, a ‘food addiction diagnosis’ will not be given, and severity of addictive eating will be classified in accordance with YFAS scoring instructions as follows: ‘mild’=3 symptoms, ‘moderate’=4–5 symptoms or ‘severe’=≥6 symptoms. The YFAS 2.0 has been found to be a robust and psychometrically sound measure of addictive eating symptomatology in non-clinical^2 67^ and clinical populations with good test/retest validity.^68^ Preliminary evidence^23 24^ suggests that YFAS scores are sensitive to change and are decreased after intervention.

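### The secondary responder analysis excludes anyone without a 3-month score and does not adjust for baseline YFAS, and the severity-class reason for its two-symptom threshold fails at baselines 8 to 11

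*Protocol article*

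**What the plan says.** All references are to the protocol article.

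- **Responder outcome** (Statistical analysis plan): "clinically significant change from baseline to 3 months, where significant requires a reduction of two or more symptoms in the YFAS". It is named as a secondary outcome.
- **Model** (same section): "This will be analysed using logistic regression with group being the only factor".
- **Missing data** (same section): "All available data will be used with no imputation of missing values at 3 and 6 months; however, baseline scores will be kept".
- **Population** (same section): "analysed according to their allocated randomisation group consistent with an intention-to-treat analysis".
- **Planned dropout** (Sample size): "allowing for a 30% dropout rate from the pilot, a sample size of 46 individuals per group (total sample size n=138) would be required". The number recruited was then set at 150, 50 per group.
- **Reason for two symptoms** (Sample size): a two-symptom fall was taken as clinically meaningful, "given this would correspond to a change in severity classification on the YFAS 2.0 tool".
- **Severity classes** (Primary outcomes): "severity of addictive eating will be classified in accordance with YFAS scoring instructions as follows", namely mild at 3 symptoms, moderate at 4 or 5, and severe at 6 or more, on a scale of 0 to 11. Entry requires at least 3 symptoms, so eligible baselines run from 3 to 11.
- **Stratification** (Randomisation and blinding): sex and mental health status.

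**The concern.** The no-imputation rule is harmless in the mixed model. There a participant with only a baseline score still contributes to the likelihood, and the analysis is valid if data are missing at random. A logistic regression of one binary change outcome on group has no such mechanism. Without a 3-month score there is no outcome, and the record drops out.

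Baseline YFAS is also likely to predict a two-symptom fall strongly, because a low score has little room to fall and a high score tends to regress. Leaving it out gives up precision, and it removes the covariate that would protect the comparison if dropout were related to severity. At stake is the one outcome that the plan labels clinically significant change.

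The threshold raises a separate question. Its stated clinical meaning can be checked against the article's own severity classes.

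**Working it through.** **1. The plan's own figures.** d = 2/2.2 = 0.91. A two-sample t-test at two-sided 0.025 with power 0.90 needs 31.27, so 32 per group. Allowing for dropout, 32/0.70 = 45.7, so 46. Both figures reproduce and are not in dispute.

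**2. Number excluded.** 0.30 × 150 = 45 excluded, leaving 105, or 35 per group. The 30% is a pilot planning figure with no time point attached, so 45 is an expectation.

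**3. Ambiguity in the missing-data sentence.** Reading the retention of baseline scores as baseline carried forward would count missing as non-response, which conflicts with no imputation. The two readings give different answers. With assumed observed response of 0.60 v 0.40 among 35 per group, responders number 21 and 14. The complete-case difference is 0.20; over 50 per group it is 21/50 − 14/50 = 0.14.

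**4. Precision.** Assume response of 0.30 v 0.60 and two-sided 0.05. Power = Φ{[Δ − 1.96√(2p̄(1−p̄)/n)] / √[(p₁q₁+p₂q₂)/n]}, with Δ = 0.30 and p̄ = 0.45.
- n = 50: (0.30 − 0.195)/0.0949 = 1.107, power 0.87.
- n = 35: (0.30 − 0.233)/0.1134 = 0.590, power 0.72.

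This is the cost of losing the records. Imputation recovers only the part that baseline and 6-month scores can predict.

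**5. Bias (illustration; inputs assumed except SD 2.2 and the two-symptom difference).** Baseline is a rounded normal with mean 6.5 and SD 2.2, kept within 3 to 11. The 3-month score has correlation parameter 0.5 with baseline and a mean fall (at baseline 6.5) of 0.5 in control and 2.5 in active. Dropout follows logit P = a + s(baseline − 6.5), with a set to give the stated rate. True response is 69% v 33%, odds ratio about 4.5. Control response rises from 7% at baseline 3 to 74% at baseline 11.

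| Dropout, active v control | Dependence on baseline | Complete-case odds ratio |
|---|---|---|
| 30% v 30% | none | 4.46 |
| 30% v 30% | same in both arms, s from −0.6 to +0.6 | about 4.5 to 4.7 |
| 20% v 40% | s = −0.4 in both | 4.0 to 4.1 |
| 20% v 40% | s = +0.4 in both | 5.1 |
| 20% v 40% | s = +0.6 in both | 5.4 |
| 30% v 30% | s = +0.4 in control only | 5.3 |

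In the second row at s = +0.4 the odds ratio is 4.57, but the response proportions become 65% and 29% instead of 69% and 33%. The last row shows that arms can differ in how dropout depends on baseline even when the rates are equal.

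For scale, the standard error of the log odds ratio with 35 per arm is √[1/(35×0.69×0.31) + 1/(35×0.33×0.67)] = 0.513. The 95% interval around 4.5 is exp(1.504 ± 1.005), about 1.65 to 12.3.

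**6. Threshold against severity class.**

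| Baseline | After a fall of 2 | Class changes? | Smallest fall that changes class |
|---|---|---|---|
| 3 (mild) | 1 (below mild) | yes | 1 |
| 4 (moderate) | 2 (below mild) | yes | 1 |
| 5 (moderate) | 3 (mild) | yes | 2 |
| 6 (severe) | 4 (moderate) | yes | 1 |
| 7 (severe) | 5 (moderate) | yes | 2 |
| 8 (severe) | 6 (severe) | no | 3 |
| 9 (severe) | 7 (severe) | no | 4 |
| 10 (severe) | 8 (severe) | no | 5 |
| 11 (severe) | 9 (severe) | no | 6 |

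The class changes from 5 of the 9 eligible scores, counting a fall below mild as a change. Two is the smallest sufficient fall at baselines 5 and 7 only.

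**The case against.** Several stronger readings are tempting, and the documents do not support them.

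- **That the result is biased under the dropout the protocol expects.** The Sample size section gives a single 30%, with no difference between arms and no link to severity. At equal rates with the same dependence on baseline, the odds ratio barely moves. The 20% v 40% split is an assumption. Even its worst case, 5.4, is small beside the interval of 1.65 to 12.3.
- **That the intention-to-treat statement is false.** The wording claims analysis by allocated group, and the plan does that. The no-imputation rule is disclosed in the preceding sentence. What is lacking is inclusion of everyone randomised in this one analysis.
- **That a group-only model is an error.** With complete data it consistently estimates the marginal odds ratio, and a prespecified unadjusted secondary analysis is legitimate. Adjustment is an improvement in power and robustness.
- **That this is the trial's main clinical result.** The article calls it secondary. The primary endpoint is the YFAS score at 3 months, analysed with all available data.
- **That the threshold has no severity meaning.** It does from baselines 3 to 7. The class rationale is given for the sample-size difference, and the responder definition reuses the number without repeating the reason.

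It can also be said that imputation details belong in a full analysis plan that is not shown. That would answer silence. Here the article fixes both the model and the no-imputation rule.

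**Conclusion.** The point stands as a moderate improvement to a secondary analysis, together with one factual correction.

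As written, the responder model excludes participants without a 3-month YFAS, about 45 of 150 if the planning dropout applies at that visit. It also leaves out baseline YFAS and the randomisation strata, all of which are already collected. Provided missingness depends only on arm and baseline, material bias in the between-arm estimate needs dropout that depends on baseline and also differs between arms, in rate or in that dependence. Differential dropout is plausible with unblinded arms of very different intensity, but no passage states it. Without it, the cost is lost precision and shifted response proportions. The odds ratios rest on the assumed baseline distribution, correlation and dropout slopes.

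The severity-class rationale is contradicted by the article's own classes for baselines 8 to 11. Correcting it changes neither the sample size nor the primary analysis.

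**What to change.** 1. Fit the responder logistic model with group, baseline YFAS, sex and mental-health stratum. Report a marginal risk difference by arm alongside the odds ratio.
2. Multiply impute missing 3-month YFAS scores within arm from baseline, 6-month score and strata, and derive response from the imputed score, so that all randomised participants are included. Keep the complete-case analysis as a sensitivity analysis. Limit the no-imputation sentence to the mixed models and say what retaining baseline scores means.
3. In the Sample size section, state that a two-symptom fall changes severity class from baselines 3 to 7 only, or justify the threshold on other grounds. Report the shift in severity class by arm descriptively.

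No new data are needed. The cost is slightly more analysis work, and a conditional odds ratio that differs from the unadjusted one, which the marginal risk difference makes easier to interpret. Imputation from arm, baseline and 6-month score still assumes missing at random, as the primary mixed model does.
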